### Safety assessment and management

The AEs are classified as mild, moderate, and severe according to the degree of impact on daily activity. The relationship between AEs and CAES is divided into five grades, including absolutely relevant, possibly relevant, possibly irrelevant, absolutely irrelevant, and immeasurably, according to the basis of the occurrence time of AEs, symptoms and changes in AEs after cassation/repetition of CAES.

Previous study has shown that CAES using long needle is a safe technique with very few AEs.^12,16^ However, possible risks should be considered for physicians who do not control the angle, direction, and depth of injection under endoscopic view as well. In general, mild AEs caused by CAES can be alleviated by themselves without special intervention. In addition to the following situations: (1) unexplained large amount of bleeding or severe pain after CAES, with ineffective conservative treatments, endoscopic examination should be taken to find etiology and do corresponding treatments; (2) rational use of antibiotics when suspected postoperative infection aggravates; (3) continuous difficulty in passing gas after CAES, enema, blinden, subcutaneous, or intramuscular injection of neostigmine will be helpful; and (4) repeat CAES or other treatment options should be adopted if symptoms are not improved significantly or even worse than before, or the recurrence of internal hemorrhoids.

In case of SAEs, treatments should be given according to the patient’s condition. Timely report to the project sponsor, ethics committee, blinding unit, regulatory authority in accordance with the Sponsor’s Standard Operating Procedures (SOPs). Site staff will be responsible for reporting SAEs and complete an SAE form. The possible most important SAEs is deep infection with pain, swollen, and redness after CAES. Antibiotics should be used in time to control the infection.

### Termination criteria

Completion of the trial or the current data are sufficient to explain the problem to be verified in this trial.

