### Proposed sample size

Sample size calculation was carried out using Stata software system (version 14.0, StataCorp, College Station, TX, USA). Assuming the proportion of patients who experienced recurrence following CAES with long injection needle is 10% and with short injection needle is 16% by reference to previous studies using sclerotherapy for internal hemorrhoids,^12,14,16,17^ the sample size required to detect a difference in the recurrence rates with 80% power and 5% significance is 525 individuals per group. To account for any between-endoscopic operator variation and follow-up loss, we propose increasing this to 578 per group (a 10% increase).

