### Outcome measures

The outcome measures and the follow-up points are shown in detail in the Supplementary Tables. The primary outcome measure is “the recurrence rate,” defined as the proportion of patients with recurrent hemorrhoids at 24 weeks post-CAES, as derived from patients’ self-reported answer to the following questions simplified by the Shanmugam and colleagues’^18^ criteria: “At the moment, do you feel your symptom (anal pain, prolapse, itching, soiling and blood loss) from your hemorrhoids are (1) cured or improved compared with before starting treatment or (2) unchanged or worse compared with before starting treatment.” Patients will be considered to have recurrent hemorrhoids when any of the following are recorded^19^: (1) “Unchanged or worse compared with before starting treatment” at 24th week as reported by the patient, or (2) seeking repeat CAES treatment, alternative non-surgical/surgical treatments for internal hemorrhoids within 24 weeks (except medication treatment), or (3) presence of any symptoms or events that strongly indicated recurrent hemorrhoids among patients not meeting (1) or (2). During follow-up, endoscopic examination will be performed when the patients develop uncontrollable anal pain, bleeding, or when repeat CAES is necessary because of recurrence.

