### Statistical analysis plan

Stata software (version 14.0, StataCorp) will be used to analyze the data. The data with the normal distribution will be presented as mean ± standard deviation, while those with abnormal distribution will be displayed as median (interquartile range [IQR]). Differences in the primary outcome measure and recurrence rate of internal hemorrhoids between the two groups will be analyzed by chi-square test. Binary logistic regression, the Wilcoxon rank-sum test, or other tests will be used to analyze the differences and the contributing factors to the possible differences between the two groups. *p* < 0.05 will be considered statistically significant.

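### The termination clause permits an undefined, data-driven early stop, which does not fit a design built on one fixed-sample test at 5%

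*Protocol article*

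**What the plan says.** Under Termination criteria the protocol article has one sentence: "Completion of the trial or the current data are sufficient to explain the problem to be verified in this trial". It gives two alternative routes to the end of the trial. The first is completion. The second depends on what the data so far show about the question under study, which the Background and Conclusion identify as long versus short needle.

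Three other places fix the design:

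- Proposed sample size: 10% recurrence with the long needle against 16% with the short needle, "with 80% power and 5% significance is 525 individuals per group", raised by 10% to 578 per group for operator variation and follow-up loss.
- Outcome measures: the primary outcome is "defined as the proportion of patients with recurrent hemorrhoids at 24 weeks post-CAES".
- Statistical analysis plan: the difference in recurrence "between the two groups will be analyzed by chi-square test", and p < 0.05 "will be considered statistically significant".

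None of these sections mentions an interim analysis, a boundary or an adjusted threshold. The second limb does not read as a safety rule either: harms are dealt with under Safety assessment and management, which contains no criterion for stopping the trial.

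**The concern.** A test at 5% keeps its error rate when the time of analysis does not depend on the results. The sample size calculation and the single significance threshold assume exactly that. The termination clause allows the end of the trial to depend on the results, without saying what would count as enough.

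Two things are at stake. If the comparison is examined more than once, and the trial may stop when it looks convincing, the chance of a false positive rises above 5%. And a trial stopped at a favourable look tends to overstate the effect, because an early look reaches significance only when the observed difference is large. The Conclusion says the result is meant to guide endoscopists, so both the p-value and the size of the difference matter. A reader of an early-stopped positive result could not confirm from this protocol that the 5% level had been kept.

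**Working it through.** **1. Is the stated sample size a single-look design?**

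Inputs from Proposed sample size: p1 = 0.10, p2 = 0.16, difference d = 0.06, mean rate 0.13, power 80% (z = 0.842), significance 5%. Sidedness is not stated; two-sided is taken (z = 1.960).

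Without continuity correction:

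n = [1.960·√(2·0.13·0.87) + 0.842·√(0.10·0.90 + 0.16·0.84)]² / 0.06² = (0.932 + 0.399)² / 0.0036 = 492.

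With continuity correction:

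n' = (n/4)·[1 + √(1 + 4/(n·d))]² = (492/4)·[1 + √(1 + 4/29.52)]² = 524.8, rounded up to 525.

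This matches the protocol exactly. One-sided versions give 388, or 421 with correction, and do not match. Then 525 × 1.10 = 577.5, rounded to 578 per arm and 1,156 in all. The 525 is a one-test figure, and the 10% is assigned to operator variation and follow-up loss, so nothing is set aside for interim looks.

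**2. Type I error if the clause were used to stop on significance**

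Assumptions that are not in the article: *sufficient* is taken to mean two-sided p < 0.05; there are K equally spaced looks, the last at 578 per arm; all patients counted at a look have their week-24 outcome; no losses. The test at each look is z = (difference in proportions) / √(2·p̄(1 − p̄)/n), whose square is the uncorrected chi-square. Both arms have true recurrence of 13%.

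| Looks | Type I error |
|---|---|
| 1 | 5.0% |
| 2 | 8.3% |
| 3 | 11% |
| 5 | 14% |
| 10 | 19% |

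These come from simulation with 200,000 trials per row. Results are almost the same with a common rate of 10% or 16%. A separate run of 1,000,000 trials per row agrees.

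**3. Estimated difference if the true rates are 10% v 16% (6.0 points)**

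| Looks | Share stopping early | Mean difference, early stops | Mean difference, all trials |
|---|---|---|---|
| 1 | none | not applicable | 6.0 |
| 2 | 58% | 7.9 | 6.5 |
| 3 | 73% | 8.0 | 6.9 |
| 5 | 82% | 8.3 | 7.4 |
| 10 | 88% | 8.9 | 8.2 |

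A hand check shows the cause. The smallest difference that reaches p < 0.05 is about 1.96·√(2·0.13·0.87/n) = 1.96·√(0.2262/n):

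- n = 116 per arm (first of five looks): 8.7 points
- n = 289 per arm (halfway): 5.5 points
- n = 578 per arm: 3.9 points

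At the first of five looks, a stop for benefit is possible only if the trial observes well over the true 6.0 points.

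**4. What happens with no look**

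One uncorrected test at 578 per arm has type I error of about 5%, power of about 86% before losses, and a mean estimate of 6.0 points.

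**The case against.** The strongest reply is that the clause is undefined, not that it prescribes repeated testing. Three stronger readings are tempting, and the article supports none of them.

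- *The trial stops at p < 0.05.* The termination section names no threshold; p < 0.05 appears only as the significance level for the analyses. Sufficient data could equally mean adequate precision, enough events or futility, and stopping for futility alone would not raise the type I error.
- *The 5% level is already lost and the estimate will be inflated.* The sample size and analysis sections plan no interim look, and completion is one of the two listed routes. The clause permits optional stopping; it does not require it.
- *Unblinded operators would judge sufficiency.* The randomisation app does show the arm to physicians, and researchers upload the endoscopy report. But no section says that operators enter the week-24 outcome, which rests first on patient self-report, or that they see results by arm or decide on stopping. No decision-maker is named at all.

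It can also be said that an article condenses a fuller protocol, and that look times, boundaries and a decision body are commonly left to documents not shown here. That is fair, and their absence is not the point. What remains is the sentence itself: it states an open-ended, data-dependent route to termination, and as written that does not fit the fixed-sample test described elsewhere in the same article.

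**Conclusion.** The point holds as an inconsistency in stated text. The termination section allows a stop short of completion, with no criterion, because of what the data show; the sample size (525 per group, reproduced exactly as a single-look calculation) and the one unadjusted threshold presuppose that no such stop occurs.

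The size of the harm is conditional. It rests on an assumed trigger (p < 0.05) and an assumed number of equally spaced looks up to 578 per arm. Over 2 to 10 looks the type I error runs from about 8% to 19%. For a true difference of 6.0 points, the overstatement runs from about 1.9 points (7.9 − 6.0) to 2.9 points (8.9 − 6.0) among trials that stop early, and from 0.5 to 2.2 points averaged over all trials. Without an interim efficacy look, both are nil.

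It should still be corrected, because an unplanned comparative look that has been acted on cannot be repaired in the analysis afterwards.

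**What to change.** Preferred: delete the second limb of the termination sentence. State that recruitment ends when 1,156 patients (2 × 578) have been randomised and that the only efficacy test is made after the last week-24 contact. The sample size, the chi-square test and the 0.05 threshold then stand unchanged.

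Alternative, if the sponsor wants the option of an early efficacy stop: prespecify the number and timing of looks, an alpha-controlling boundary and who decides. One example is a single look at half the information with an O'Brien-Fleming boundary, |z| > 2.80 at the interim and |z| > 1.98 at the end (nominal p about 0.005 and 0.048). These follow from a constant of 1.977: 1.977·√2 = 2.80 halfway and 1.98 at the end. In simulation this pair holds the overall level at 5.0%. A boundary protects the error rate, not the estimate, so this option should also name a bias-adjusted estimate for use after an early stop.

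Cost: one sentence in an amendment for the preferred option, a short paragraph for the alternative. What the sponsor gives up is the freedom to stop early at will.

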### Statistical analysis plan

Stata software (version 14.0, StataCorp) will be used to analyze the data. The data with the normal distribution will be presented as mean ± standard deviation, while those with abnormal distribution will be displayed as median (interquartile range [IQR]). Differences in the primary outcome measure and recurrence rate of internal hemorrhoids between the two groups will be analyzed by chi-square test. Binary logistic regression, the Wilcoxon rank-sum test, or other tests will be used to analyze the differences and the contributing factors to the possible differences between the two groups. *p* < 0.05 will be considered statistically significant.

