### Randomization

A remote, web-based randomization system (Medical Data, Unimed Scientific, Inc, Wuxi, China) will be used to generate random numbers for the participants. Patients will be divided into the long injection needle group (n = 578) and the short injection needle group (n = 578) at a ratio of 1:1 according to the random numbers. The Medical Data application program (APP; System developed by Unimed Scientific, Inc, Wuxi, China) will directly display the randomly assigned treatment group to instruct physicians to select injection needles for CAES.

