**Figure 4. fig4-2631774520925636:**
[figure not shown]
The operation steps of CAES. (a) A full scale of colonoscopy is recommended prior to CAES. (b) The injection needle is advanced to the targeted points through the endoscopic channel to inject the sclerosing agent. (c)–(e) Then choose the injection sites in clockwise order.

**Table 1. table1-2631774520925636:** The differences of CAES based on the long and short injection needle.

Items	Long injection needle	Short injection needle
Endoscope	Colonoscope	Colonoscope; gastroscope if retroflection of the endoscope is necessary
Cap	Straight and short	Straight and short
Length of the needle	14 mm	4 mm
Direction of endoscope	Anterograde	Anterograde, retroflection sometimes
Injection position	Above the dentate line	Above the dentate line, the oral side or middle of hemorrhoids
Targeting location	Longitudinal submucosal layer for 14 mm length	Submucosal layer for one point-like bump
Retracting needle	Injecting during retracting the needle	Injecting without retracting the needle
Injection methods	Change injection sites clockwise without tracer, 0.5 to 2.0 mL for each site	Change injection sites clockwise with or without tracer, 0.5 to 2.0 mL for each site
Presumed therapeutic role	Hemostasis and treatment for prolapse	Hemostasis

CAES, cap-assisted endoscopic sclerotherapy.

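### The primary recurrence comparison is fixed as an unadjusted chi-square test; a prespecified model with haemorrhoid grade and centre or operator would gain modest precision without extra patients

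*Protocol article*

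**What the plan says.** - **Primary test (Statistical analysis plan).** "Differences in the primary outcome measure and recurrence rate of internal hemorrhoids between the two groups will be analyzed by chi-square test". No centre, operator, grade or baseline value is mentioned in connection with this test.
- **Other methods (same section).** "Binary logistic regression, the Wilcoxon rank-sum test, or other tests" are listed for examining differences and the factors behind them. None is tied to a particular outcome or covariate.
- **Sample size (Proposed sample size).** Recurrence of 10% (long needle) v 16% (short needle), "with 80% power and 5% significance is 525 individuals per group". Then: "To account for any between-endoscopic operator variation and follow-up loss, we propose increasing this to 578 per group", described as a 10% increase.
- **Allocation.** Patients are individually randomised (text under Figure 2), "at a ratio of 1:1 according to the random numbers" (Randomization).
- **Grade.** Grades I to III are eligible, with grade III entering under different conditions (Inclusion criteria). Grade I is defined by the absence of prolapse (Classification of internal hemorrhoids).
- **Presumed mechanism (Table 1).** Long needle: "Hemostasis and treatment for prolapse". Short needle: haemostasis only.
- **Timing (text under Figure 2).** Data are collected before the procedure and up to week 24. The schedule by item is in figures and supplementary tables that are not shown.

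**The concern.** By the protocol's own account, two things could move recurrence besides the needle: the operator and the grade. Prolapse is one of the symptoms in the primary outcome question. If only the long needle acts on prolapse, grade may predict the outcome and may also change the size of the needle effect. A pooled chi-square test uses neither piece of information. What is at stake is some precision on the primary outcome, protection against chance imbalance in grade, and a planned look at whether the needle effect is similar with and without prolapse.

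The operator issue is named in the sample size section, but the stated primary test has no place for it and the sample size has no allowance of its own for it.

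**Working it through.** **1. The plan's own figures.** Inputs from Proposed sample size: p1 = 0.10, p2 = 0.16, difference d = 0.06, mean 0.13, 80% power, 5% significance (taken as two-sided).

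- Uncorrected: n = [1.96·√(2·0.13·0.87) + 0.8416·√(0.10·0.90 + 0.16·0.84)]² / 0.06² = (0.9322 + 0.3987)² / 0.0036 ≈ 492.
- With continuity correction: n′ = (n/4)·[1 + √(1 + 4/(n·d))]² = (492/4)·(1 + √1.1355)² ≈ 525. This matches the stated figure.
- Increase: 525 × 1.10 = 577.5, rounded up to 578. This also matches.

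**2. What the 10% increase covers.** The protocol does not divide it between operators and loss. If loss alone were 10% (an assumption), 578 × 0.90 = 520 per group would remain, 5 short of 525, with nothing left for operators. Power without continuity correction is 85.9% at 578, 82.5% at 525 and 82.1% at 520.

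**3. Power with and without adjustment.** The article gives no number of operators, no between-operator variance and no prognostic strength, so the following settings are assumptions: 520 per group, 10% v 16%, 40 operators, normal operator and covariate effects on the logit scale, 4,000 runs per row. The Monte Carlo standard error is about √(0.83·0.17/4000) = 0.6 points.

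| Operator SD | Covariate SD | Chi-square | Logistic with covariate | Stratified by operator only (Cochran-Mantel-Haenszel) |
|---|---|---|---|---|
| 0 | 0 | 83.6% | 83.5% | 81.9% |
| 0.3 | 0.5 | 82.3% | 83.3% | 80.8% |
| 0.5 | 0.5 | 83.1% | 83.8% | 82.2% |
| 0.5 | 1.0 | 81.9% | 85.6% | 81.2% |
| 0.8 | 0.8 | 82.3% | 84.3% | 83.0% |

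Covariate adjustment changes power by −0.1 to +3.7 points. Operator stratification alone changes it by −1.7 to +0.7 points.

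A second set of runs adjusted for grade and centre together (assumed: 20 centres, 35% grade III, grade odds ratios 2 to 4, centre SD 0.4 to 0.8; 1,500 runs). Power went from 83.5% to 84.1%, from 82.1% to 84.5% and from 82.5% to 85.3%, gains of 0.6, 2.4 and 2.8 points.

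**4. Validity of the chi-square test.** Under no needle effect (13% in both groups), with operators differing only in overall recurrence level, it rejected in 4.9% to 5.3% of runs, which is nominal. With an assumed needle-by-operator interaction (SD 0.3 and 0.5), the rates were:

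- chi-square: 5.8% and 6.4%
- logistic with covariate: 5.8% and 6.7%
- stratified by operator: 5.6% and 7.0%

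Separate runs at SD 0.3 gave 6.2% for the chi-square with 60 operators and 7.4% with 20. Neither ordinary adjustment nor stratification removes this excess.

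**5. Scores.** For a continuous score with baseline-to-follow-up correlation r, baseline adjustment multiplies the variance by 1 − r². The reduction is 4% at r = 0.2, 9% at 0.3, 25% at 0.5 and 49% at 0.7. All of these correlations are assumed.

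**The case against.** The strongest reply is that nothing here is wrong. Under individual randomisation an unadjusted chi-square test is valid, it matches the two-proportion calculation behind 525, and every simulated power above exceeds the planned 80%. The gain is small, and in the first set of runs it disappears when the covariate is not prognostic. All of that stands and sets the weight of the point.

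Several stronger readings are tempting but are not supported:

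- *The symptom and quality-of-life scores will be compared by a rank-sum test that ignores baseline.* The rank-sum test is one of several options and is assigned to no outcome. Baseline recording of the scores is a fair inference from data collection before the procedure, but the item schedule is not shown.
- *Operator variation will be modelled nowhere.* Logistic regression for contributing factors is planned and could include operator or grade. An article may leave the choice of covariates to a fuller plan.
- *Allocation is unstratified.* The article neither describes nor excludes strata in the web system, and its silence proves nothing.
- *The chi-square test inflates type I error and adjustment repairs it.* The excess needs an assumed needle-by-operator interaction, and the adjusted and stratified analyses showed it too.
- *Grade must change the needle effect.* Table 1 labels the therapeutic roles as presumed. This is a reason to examine the contrast, not evidence of an interaction.

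What the reply does not remove is that the article does more than stay silent: it fixes the primary test, and a better one is available from data already known at entry.

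**Conclusion.** The point holds as a free improvement. The stated primary analysis is valid but forgoes modest precision: about 0 to 4 power points at 520 per group, depending on assumed prognostic strength and operator or centre variation. The gain comes mainly from grade or another prognostic baseline covariate and not from operator stratification alone. Including centre or operator is still sensible because the protocol itself names that source of variation and offers only a shared 10% increase against it.

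For the scores the gain could be larger, for example 9% less variance at r = 0.3 and 25% at r = 0.5. That applies only where baseline values are recorded, and it is measured against an unadjusted comparison that the article does not commit to.

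**What to change.** 1. **Primary analysis.** Prespecify a logistic regression of recurrence on needle, with grade (I/II/III) as covariate and centre or operator as random effect or stratum. Report a standardised risk difference with 95% CI, so that the result stays on the scale of the 10% v 16% planning assumption. With about 52 + 83 = 135 expected recurrences at 520 per group (520 × 0.10 and 520 × 0.16), 40 operators (assumed) would average about 3.4 events each. A random effect would then be safer than a separate fixed term for each operator.
2. **Supportive analysis.** Keep the chi-square test.
3. **Secondary analysis.** Prespecify a needle-by-grade contrast. By the protocol's definitions, the split between no prolapse and prolapse lies between grade I and grades II-III. The sample size was not set for an interaction, so report an estimate with its interval.
4. **Scores.** Where symptom score and EQ-5D are recorded before the procedure, analyse week-24 values by regression on needle, baseline value and grade.

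The cost is wording in the analysis plan, settled before unblinded data are seen so that covariates are not chosen afterwards. No patients, visits or new data are needed.
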